## Abstract

**Background:**

Adherence to antiplatelet medications is critical to prevent life threatening complications (ie, stent thrombosis) after percutaneous coronary interventions (PCIs), yet rates of nonadherence range from 21-57% by 12 months. Mobile interventions delivered via text messaging or mobile apps represent a practical and inexpensive strategy to promote behavior change and enhance medication adherence.

**Objective:**

The Mobile4Meds study seeks to determine whether text messaging or a mobile app, compared with an educational website control provided to all Veterans, can improve adherence to antiplatelet therapy among patients following acute coronary syndrome (ACS) or PCI. The three aims of the study are to: (1) determine preferences for content and frequency of text messaging to promote medication adherence through focus groups; (2) identify the most patient-centered app that promotes adherence, through a content analysis of all commercially available apps for medication adherence and focus groups centered on usability; and (3) compare adherence to antiplatelet medications in Veterans after ACS/PCI via a randomized clinical trial (RCT).

**Methods:**

We will utilize a mixed-methods design that uses focus groups to achieve the first and second aims (N=32). Patients will be followed for 12 months after being randomly assigned to one of three arms: (1) customized text messaging, (2) mobile app, or (3) website-control groups (N=225). Medication adherence will be measured with electronic monitoring devices, pharmacy records, and self-reports.

**Results:**

Enrollment for the focus groups is currently in progress. We expect to enroll patients for the RCT in the beginning of 2018.

**Conclusions:**

Determining the efficacy of mobile technology using a Veteran-designed protocol to promote medication adherence will have a significant impact on Veteran health and public health, particularly for individuals with chronic diseases that require strict medication adherence.

**Trial Registration:**

ClinicalTrials.gov NCT03022669

## Introduction

### Coronary Heart Disease and Medication Adherence

Coronary heart disease is the leading cause of death in Veterans and affects 15.5 million people in the United States [1,2]. Although coronary heart disease claims the lives of one out of every seven Americans [2], the decline in acute coronary syndrome (ACS) and coronary heart disease-related deaths over the past four decades has been attributed to the availability of critical pharmacologic and invasive therapies (ie, percutaneous coronary intervention [PCI]) [3-6]. After PCI with drug-eluting stents, premature discontinuation of antiplatelet (thienopyridine) medications is strongly associated with in-stent thrombosis, leading to myocardial infarction (MI) and death [7,8]. Despite the critical nature of taking antiplatelet medications to prevent life-threatening complications, one in seven MI patients treated with drug-eluting stents no longer take antiplatelet medications at 30 days [8].

Medication nonadherence is a pervasive public health problem among Veterans and non-Veterans [9-12]; however, Veterans suffer from increased morbidity and mortality from chronic diseases compared to non-Veterans [13]. Medication nonadherence is the number one problem in treating illnesses, as more than half of individuals with chronic diseases do not take any or all of their medications correctly [14,15]. Medication nonadherence in patients with coronary heart disease is closely linked to adverse clinical outcomes such as rehospitalization and mortality [16-18]; therefore, effective strategies are needed to improve adherence behaviors. Moreover, medication nonadherence results in an estimated US $290 billion in health care costs in the United States and is a tremendous burden on the health care system [19]. Mobile technology may represent an effective strategy to improve medication adherence during the critical time period of one year post-ACS/PCI.

### Mobile Health

In the past decade, mobile health (mHealth) has been introduced as a mechanism to enhance medication adherence and demonstrates strong potential to promote behavior change. The use of technology can facilitate adoption and integration of medication adherence by promoting behavioral strategies via health messaging, emphasizing healthy habits, tracking goals, and giving incentives for behavior change [20]. While other behavioral and educational strategies have had disappointing results in adherence and treatment outcomes over many decades [21,22], the use of technology may provide an innovative, practical, personalized, and inexpensive approach to promote medication adherence. Diverse solutions are required with tailored theory-based interventions for different populations and conditions because the reasons for medication nonadherence are complex and multifactorial [23,24]. Experts agree that a patient-centered approach is critical to increase patients’ knowledge about medication management [25].

Both text messaging and mobile apps are two popular forms of mHealth that provide convenient, inexpensive, and nonintrusive engagement with individuals. The use of mobile technology can particularly benefit those who have significant barriers to taking medications, such as confusion about which medications to take, forgetfulness, and lack of social support. Text messaging is more widely used by all age groups; however, mobile apps offer many more features than text messaging, and can harness the full sensing and computational capacity of mobile devices to collect and analyze health-related data in real time to deliver health and behavioral interventions [20,26].

Text messaging is popular, fast, direct, efficient, user-friendly, traceable, and provides easy data transfer [27]. Text messaging is also nonintrusive, relatively simple, and lower in cost compared to mobile voice communication [28]. In a systematic review of medication adherence studies using text messaging, we found that most interventions (18/29) resulted in improved medication adherence [29]. This review did not examine any studies related to coronary heart disease, but gaps in the literature were discussed, such as understanding factors that are needed to maintain engagement (eg, content and frequency of text messaging). In contrast to text messaging, apps can offer interactivity, gaming, and feedback. Apps have the advantages of delivering interventions to an unlimited number of individuals in a cost-effective manner with favorable cost utility [30]. While Internet interventions can be delivered via traditional desktop and laptop computers, users have the capacity to interact with mobile interventions more frequently and in the context of the behavior of interest [31]. The trend of desktop use for research/program interventions is sharply declining in our current generation, given that most people carry and access their mobile phones throughout the day for various reasons. Using real-time sensing technologies available on mobile phones, health behavioral change interventions can be delivered based on time/location, psychological state, physiological state, social context, activity level, and patterns [32].

### Preliminary Studies

In a pilot randomized controlled trial (RCT) from 2012-2013, we compared antiplatelet and statin adherence among patients with coronary heart disease in a 30-day study who received: (1) text messaging for medication reminders and education, (2) educational text messaging only, or (3) no text messaging [33]. Among 90 patients (76% male, mean age 59.2 years), electronic devices revealed that patients who received text messaging for antiplatelets had a higher percentage of correct doses taken (*P*=0.02), percentage number of doses taken (*P*=0.01), and percentage of prescribed doses taken on schedule (*P*=0.01) [33]. Text messaging response rates were higher for antiplatelets than statins (*P*=0.005), and self-reported adherence revealed no significant differences among groups [33]. We concluded that the use of text messaging for the medication reminders/education and education text messaging only groups (compared to no text messaging for the control group) increased adherence to antiplatelet therapy by 15% to 17%, respectively. We established feasibility and high satisfaction and concluded that mHealth interventions show promise in promoting medication adherence.

### Aims

The proposed research study, Mobile4Meds, seeks to determine whether text messaging or a mobile app (compared with an educational website control provided to all Veterans) can improve adherence to antiplatelet therapy among patients post-ACS/PCI. There are three topics and aims of this proposed study. First, using *Text Messaging* we aim to determine preferences for content and frequency of text messaging to promote medication adherence. Second, using *Mobile Apps* we aim to identify the most patient-centered (user-friendly, engaging, personalized) mobile app that promotes medication adherence with stratification by low/high mobile phone use and sex. Finally, we aim to examine *Medication Adherence* by comparing adherence to antiplatelet medications upon hospital discharge from ACS/PCI via: (1) text messaging, (2) mobile app, or (3) website-control. Figure 1 illustrates the aims, objectives, and outcomes of the proposed research study. Our long-term goal is to conduct a multi-site full scale RCT to determine clinical outcomes of emergency department utilization, rehospitalization, and cardiovascular (and all-cause) morbidity and mortality.

**Figure 1 figure1:**
[figure not shown]
Aims, objectives, and outcomes.

## Methods

### Theoretical Framework/Behavioral Change Model

To date, most mHealth studies have not been based on behavioral health theories [29,31]. In a systematic review of text messaging studies on medication adherence in various acute and chronic conditions, we found that only 5 of 29 studies used theory to guide research [29]. Numerous precipitating factors and barriers affect medication adherence, and this complex process can be better understood when examining theoretical relationships and process. The conceptual model that explains the relationship between variables in this study is depicted in Figure 2. No single theory can completely explain the processes that lead to medication adherence, so we will use a theory-informed approach to complete the aims for this study. We will explore the general components of theory that are closely linked with behavioral change interventions (eg, perceived norms/threats, health beliefs, self-efficacy, cues to actions).

**Figure 2 figure2:**
[figure not shown]
Conceptual model of behavior change for medication adherence.

**Figure 3 figure3:**
[figure not shown]
Overview of study structure and sample. FG: focus group.

### Research Design

Mobile4Meds is a mixed-methods study using both qualitative and quantitative research methods. Engaging patients initially through qualitative methods will provide opportunities for: (1) better translation, dissemination, and use of research results; (2) better evidence to inform guidelines; (3) targeted quality improvement; and (4) using research to address concerns of diverse patients [34]. Figure 3 provides an overview of the study structure and participants involved in each of the aims.

### Aim 1: Text Messaging Focus Groups

#### Design, Sample, Setting

We will use focus groups to fulfill the objectives of Aim 1. Each focus group will have 6-8 participants, which is a size that allows for easy exchanges of ideas and a diversity of perspectives to be represented. We will recruit a convenience sample of 24-32 participants for four focus groups. Aims 1 and 2 will include the same participants who will attend a total of four focus group sessions (Figure 3).

The participants from San Francisco Veterans Affairs Medical Center (SFVAMC) are likely to be predominantly male; therefore, we will likely recruit one group of female Veterans from SFVAMC and one focus group of female non-Veterans from John Muir Medical Center (JMMC) in the East Bay. The four groups will account for variability in mobile phone use (low/high) and sex. Inclusion criteria for Aims 1 and 2 include: (1) >21 years of age, (2) history of ACS or PCI within one year, and (3) current/former antiplatelet (thienopyridine) prescription. Exclusion criteria are: (1) cognitive impairment, and (2) lack of English proficiency/literacy.

#### Methods

##### Preliminary Development of Text Messaging

We will explore different content for the development of a text messaging intervention to determine the ideal tailored messages for delivery in the RCT (Aim 3). After studying various behavioral change theories and frameworks, we will create a text messaging intervention with the underpinnings of common behavioral change theories. A library of 80-100 sample text messages that apply personalized content will be created to enhance medication adherence. We found that education alone increased medication adherence in prior studies, so we will deliver cardiovascular risk reduction messages along with messages regarding medications. Topics will include medications, diet, exercise, risk factors for coronary heart disease (eg, smoking, obesity), depression, stress management, and preventive care. Participants will choose the frequency and timing of text messaging. An example of an automated medication text messaging may be, “John, take your Plavix 75mg at 9am. Confirm with 1.”

##### Recruitment

We will distribute written materials such as flyers and brochures to advertise voluntary participation in the research study. The research team (principal investigator and research assistant [RA]) will consult with the cardiac rehabilitation staff at SFVAMC and JMMC to identify individuals who are willing to participate in a research study. The research team will meet with interested individuals and provide verbal and written explanation of the study. Participants will sign a written informed consent document.

##### Group Assignment

Upon recruitment into the study, participants will complete a sociodemographic questionnaire and a brief survey that will determine if he/she is a *low* or *high* mobile phone user. Separating participants into groups will help facilitate identification of common ideas and goals that low/high mobile phone users and men/women may address during the focus groups. We will use maximum variation sampling to ensure variability in age, gender, ethnicity, and low/high mobile phone use.

##### Focus Groups

In Aim 1, the focus group sessions will address ideal content and frequency of text messaging. First, we will give an introduction of the study aims and purpose of the focus group. Second, we will discuss the needs, preferences, perceived facilitators, and perceived barriers of using text messaging for medication adherence. Third, we will review sample text messaging, and we will ask participants which content and frequency of text messaging are the most effective and least intrusive. Finally, all participants will be able to suggest text messaging to create the most personalized messages.

##### Data Collection

All focus groups will be audiotaped, and the RA will take field notes on individual and group reactions that are not captured by the recording. We will complete field notes at the conclusion of each session, and all sessions will be transcribed verbatim.

#### Analysis

Thematic analysis will include reading and coding the completed field notes and interview transcripts. We will create an initial set of codes that account for the study aims and other topics that emerge from the data. Some codes will be generated deductively, while others will be generated inductively based on themes and issues that emerge from ongoing coding. We will compare coding, resolve differences, and revise the coding scheme. We will assess intercoder reliability by having 10% of the data cross-coded. The key outcomes will be content and frequency of text messaging, particularly focusing on how preferences vary across groups. We will use ATLAS.ti (Thousand Oaks, CA) for all qualitative analyses to determine the preferred app for Aim 3.

### Aim 2: Mobile Apps: Focus Groups

#### Design, Sample, and Setting

Aim 2 consists of Aim 2a (*content analysis*) and Aim 2b (*usability testing*). The usability study will include the same individuals from the focus groups in Aim 1 who are stratified by low/high mobile phone use and sex, to accommodate easy exchanges of ideas and a diversity of perspectives. In contrast to Aim 1, there will be three focus group sessions to fulfill Aim 2. Recruitment, group assignment, and data collection will be the same for Aim 2a and Aim 2b.

##### Aim 2a – Content Analysis

###### Methods

We will conduct a content analysis approximately three months prior to the focus groups. The first phase will involve a comparative, descriptive assessment of smartphone apps in the categories of health and medications. To ensure a comprehensive search, the research team will search for medication adherence-oriented apps, provider websites, and app sources that are available in Apple iTunes, Android Marketplace, and Blackberry App World Store.

We will provide a comparative, descriptive assessment of the top 10 smartphone apps related to medication adherence. The content analysis will examine whether each app applies constructs from behavioral change theory. We will assess each of the selected apps using a validated behavioral theory content survey by Doshi et al [35]. The survey assesses the presence of essential constructs of four major theories of behavior change: Health Belief Model, Transtheoretical Model, Theory of Reasoned Action/Planned Behavior, and Social Cognitive/Social Learning Theory [35]. After content analysis is completed, we will rank the top 10 medication adherence apps and record usability, application of theory, user reviews, star ratings, and the total number of downloads.

###### Analyses

We will analyze the content analysis by following the scoring instructions of the Behavioral Theory Content Survey for the top 10 mobile apps [35]. The Behavioral Theory Content Survey will include 20 items from the following domains listed in Table 1. Mean survey score and standard deviation (SD) will be computed across the top 10 apps based on a total of 20 items from the 5 domains, each accounting for 1 point (yes=1, no=2) [35]. We will then provide a descriptive evaluation of the apps based primarily on survey scores (mean, SD) and subsequent rankings [36]. Interacting with the mobile app will include a dynamic process of iterative adjustments in response to user input, key features, and functionality that may not be apparent upon initial use and subsequent input [36].

**Table 1 table1:** Behavioral strategies included in the Behavioral Theory Content Survey [35,36].

Domain	Example
1. Knowledge	General information
2. Cognitive strategies	Perceived benefits/barriers/risks, self-efficacy
3. Behavioral strategies	Self-monitoring, time management, social support
4. Emotion-focused strategies	Stress management
5. Therapeutic interventions	Motivational readiness

##### Aim 2b - Usability Testing: Methods

###### Mobile App Focus Groups – Session 1 (Formative Stage)

After the research team identifies the top 10 medication reminder apps through content analyses, the focus group for Session 1 will help to determine the top 2-4 apps the participants will use for one week at a time. Four different groups will be stratified by low/high mobile phone use and sex (Figure 3). We will briefly demonstrate the apps for participants on a large screen and ask participants to engage with the preloaded apps on our research smartphones. We will assess participants’ impressions of the apps and ask them to score the apps (range 1-5) so we can determine the ideal number of apps to trial from the distribution of rankings. Participants’ comments and overall scores will help determine the preferred apps.

###### Session 2 (Exploratory Stage)

During the focus group for Session 2, the majority of time will be spent on group assessment of overall experience with mobile apps in general. After the group assessment, we will include introduction of the preselected apps from Session 1. The selected apps from Session 1 will be downloaded to the patients’ mobile phones devices. Patients will spend approximately 10-15 minutes experimenting with and evaluating the selected apps. We will conduct observations of patients as they interact with the mobile apps. Participants will be randomly assigned to use the first app in Session 2 and use that app for one week, then switch to the other app(s) in subsequent weeks. Figure 3 displays a scenario in which participants will be randomly assigned to use two mobile apps for two weeks; however, participants may trial between 2-4 mobile apps for one week each, depending on the results of the Mobile App Session 1 focus groups.

Participants will record impressions in a diary while using the apps. We will contact the participants by text/email/ phone-call/visit within two days after using each mobile app to troubleshoot any difficulties. At the start of each week, we will contact participants to remind them to switch over to the next mobile app.

###### Session 3 (Usability Stage)

After the trial period with mobile apps, the focus group for Session 3 (which assesses usability) will include: (1) follow-up on patients’ experience and preferences with using the selected mobile apps, and (2) completion of a 10-item System Usability Scale to provide a quantitative evaluation of the mobile apps to supplement the focus groups and interviews [37]. A winning app will be selected for the RCT.

##### Usability Testing: Analysis

The three focus group sessions for Aim 2 will be transcribed, coded, and analyzed in the same manner as in Aim 1. The System Usability Scale used in the Mobile App Session 3 focus group will yield a single number from 0 to 100 representing a composite measure of the overall usability of mobile apps being tested [37]. The scale will be scored as directed by the original authors.

### Aim 3: Medication Adherence Randomized Controlled Trial

#### Design

The research design for Aim 3 is an RCT that lasts 12 months. In contrast to Aims 1 and 2 that included participants who were post-ACS/PCI within one year and recruited from a cardiac rehabilitation program, participants for Aim 3 will be recruited from the hospital after ACS/PCI.

#### Sample Size Estimation

We plan to enroll 225 total participants (75 participants per group). Allowing for a 15% attrition rate over the 12-month study, we conservatively estimate that this recruitment target will result in a total sample size of n=192, which will give 86% power to detect a medium effect size (half-SD difference) between at least one treatment group and the control group using Dunnett’s method to adjust for multiple comparisons. This sample size would give more than 95% power to detect an effect size of d=0.69, as found in our previous clinical trial [33]. Analysis of the longitudinal data points with mixed-effects models will confer additional power.

#### Sample

The convenience sample will consist of 159 male and female Veterans from SFVAMC and 66 female participants (29% of sample) from JMMC. A sample size of 225 is considered to be feasible considering the number of post-ACS/PCI patients who are treated at both institutions. We have incorporated a 29% oversample of women to ensure a sufficient sample size to examine subgroup differences in intervention effects, given the low enrollment of female Veterans in Veterans Health Administration (6%) [38]. Inclusion criteria include: (1) >21 years of age, (2) recent ACS or PCI within one week, and (3) new antiplatelet (thienopyridine) prescription. Exclusion criteria are: (1) cognitive impairment, and (2) lack of English proficiency/literacy. For the process evaluation, we will recruit a subset of 10 participants from each experimental group (text messaging and mobile app; total n=20) for in-depth individual interviews.

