#### Intervention

We will conduct an RCT with random assignment to one of three groups: (1) text messaging, (2) mobile app, or (3) website-control, for a total of 12 months. Both intervention groups will also be offered the patient education website that the control group will be given. The *text messaging group* will receive text messages with content and frequency informed by Aim 1. We will use the Veterans Affairs (VA) *Annie* text messaging program. For non-Veteran females, we will use a text messaging program from CareSpeak Communications. The *app group* will use the preferred app that is selected in Aim 2. The major purpose of the app is to remind participants to take medications; however, the app will likely include other features such as providing educational messages. The *website group* will be offered the American Heart Association patient education website (My Life Check - 7 Steps To Healthy Living) and will serve as an active control group [43]. The website will be offered to participants in all three groups. The *7 small steps to big changes* are to manage blood pressure, control cholesterol, reduce blood sugar, get active, eat better, lose weight, and stop smoking.

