#### Primary Statistical Analysis

Our primary analysis will use a mixed-effects linear model. The predictors will be a categorical predictor of group (with control as reference), time, and the group-by-time interactions, as well as the recruitment site (SFVAMC vs JMMC), as randomization is stratified by site. The parameters in the group-by-time interaction are the primary parameters of interest, describing whether adherence changes differentially over baseline in each of the treatment groups compared to the control group. We will also investigate whether other models for change over time are more appropriate, including arbitrary means or nonlinear time functions through comparison of Akaike information criterion/Bayesian information criterion. Secondary analyses will adjust for select covariates that are strongly associated with adherence.

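### The women recruited at JMMC do not give a sufficient sample for a sex-by-treatment effect: sex overlaps heavily with site and Veteran status, and the detectable interaction is about 1 SD

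*Protocol article*

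**What the plan says.** The Sample section of Aim 3 sets the composition: "The convenience sample will consist of 159 male and female Veterans from SFVAMC and 66 female participants (29% of sample) from JMMC". It gives the purpose: "We have incorporated a 29% oversample of women to ensure a sufficient sample size to examine subgroup differences in intervention effects". The same sentence justifies the oversample by the 6% share of women in Veterans Health Administration enrollment. It gives no male-female split for the 159 SFVAMC participants.

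The Primary Outcome section identifies the JMMC participants as non-Veteran women. Two procedures differ for them. Veterans in the text arm use the VA Annie program, but the Intervention section says "For non-Veteran females, we will use a text messaging program from CareSpeak Communications". Refill data come from Peoplechart at JMMC and from the VA Corporate Data Warehouse at SFVAMC.

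Randomization is stratified by site. The primary model contains group, time and group-by-time, "as well as the recruitment site (SFVAMC vs JMMC), as randomization is stratified by site". The only power figures, in Sample Size Estimation, concern the overall comparisons with control.

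**The concern.** The protocol states a property of the sample, and two conditions are needed for it to be true. The contrast between women and men must be interpretable as a difference by sex, and the numbers must be large enough to estimate it usefully.

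The recruitment structure undermines the first. One site enrolls no men, so the female-male contrast is largely a contrast between two hospitals and between non-Veterans and Veterans. In the text arm it is also a contrast between two messaging programs. The site term in the primary model is a main effect: it adjusts the level of adherence and does not separate treatment-by-sex from treatment-by-site.

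The second is a matter of arithmetic, shown below. At stake is the reading of the result. A difference due to health system or platform could be reported as a sex difference, or a non-significant interaction could be taken as evidence that the interventions work equally well in both sexes.

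**Working it through.** **Inputs.** From Sample Size Estimation: "We plan to enroll 225 total participants (75 participants per group"; "Allowing for a 15% attrition rate over the 12-month study"; target difference 0.5 SD. From Sample: 159 at SFVAMC, 66 women at JMMC. Assumptions of this check: two-sided alpha of 0.05, and a female share *p* at SFVAMC of 6% (range 0 to 20%).

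**Step 1: the plan's own figure.** The protocol says of n=192: "which will give 86% power to detect a medium effect size (half-SD difference) between at least one treatment group and the control group", with Dunnett's adjustment. With 64 per group, 189 degrees of freedom, a two-sided Dunnett critical value of 2.23 and both treatments shifted by 0.5 SD, simulated any-pair power is 86.2%. At d=0.69 it is 98.8%, in line with the stated figure above 95%. The plan's main-effect power reproduces.

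**Step 2: overlap of sex and site.** Women W = 66 + 159*p*; men M = 159(1 − *p*). As JMMC has no men, the correlation (phi) between sex and site is √[66M / (159W)].
- *p* = 6%: W = 75.5, M = 149.5; phi = √[66 × 149.5 / (159 × 75.5)] = 0.91; 66/75.5 = 87% of women are at JMMC.
- *p* = 0, 10%, 20%: phi = 1.00, 0.85, 0.73.

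**Step 3: detectable interaction.** For one active arm versus control, in SD units, SE = √(2/w + 2/m), where w and m are women and men per arm. The interaction detectable at 80% power is (1.96 + 0.84) × SE.
- w = 75.5 × 0.85 / 3 = 21.4; m = 149.5 × 0.85 / 3 = 42.3.
- SE = √(2/21.4 + 2/42.3) = 0.375.
- Detectable interaction = 2.80 × 0.375 = 1.05 SD.
- Power at 0.5 SD = Φ(0.5/0.375 − 1.96) = 0.265, about 27%.
- Power at 0.69 SD, the effect in the earlier trial, is 45%.

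**Step 4: sensitivity.**

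| Variation | Detectable at 80% power |
|---|---|
| *p* from 0 to 20%, with or without attrition | 0.92–1.09 SD (power at 0.5 SD: 25–33%) |
| Base case, Dunnett critical value | 1.15 SD |
| Base case, both active arms pooled against control | 0.91 SD |
| Base case, three visits averaged, assumed within-person correlation 0.3, 0.5, 0.7 | 0.77, 0.86, 0.94 SD |
| No oversample: 225 Veterans, 6% women, 15% attrition | 2.1 SD |

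The averaging row multiplies 1.05 by √[(1 + 2ρ)/3]. It applies only if the SD is that of a single visit; if the SD is that of the 12-month aggregate, there is no gain.

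**Step 5: removing site.** Once a treatment-by-site term is added, only SFVAMC informs treatment-by-sex. At *p* = 6% that leaves 159 × 0.06 × 0.85 / 3 = 2.7 women per arm and a detectable interaction of about 2.5 SD.

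**The case against.** The strongest reply is that the sentence promises only to examine subgroup differences. It announces no powered interaction test and no attribution to sex, and the modelling and the exploratory label may stand in a full protocol or analysis plan that is not shown. It is fair not to fault the article for omitting the subgroup model. But the sentence does assert sufficiency, and no later plan can cleanly separate sex from site when one site enrolls no men. The sentence does not name sex as the subgroup variable, but an oversample of women has no other plain meaning.

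Several stronger readings are tempting and should be resisted.
- *Sex and site are almost completely confounded.* This depends on how few women SFVAMC enrolls, which the article does not say. The 6% describes Veterans Health Administration enrollment, not this sample; at 20% the correlation falls to 0.73.
- *Platform and refill source distort every comparison.* Platform bears only on text messaging versus control; the app and website are not said to differ by site. Refill source concerns secondary outcomes. The primary MEMS endpoint is the same at both sites.
- *Nothing can be learned about women.* Randomization is stratified by site, so the treatment effect among JMMC women is a valid randomized estimate. Only the explanation of a difference from SFVAMC is ambiguous.
- *Effects below 1 SD cannot be detected.* The figure is an 80% power threshold, not a limit. Pooling arms or averaging visits lowers it to roughly 0.8 to 0.9 SD, still well above 0.5.
- *Power among Veterans falls from 86% to 56%.* These figures are on different bases. With 159 × 0.85 / 3 = 45 per arm, 56% is power per comparison at d=0.5, for which the full sample has about 73%. On the protocol's any-pair basis the Veteran-only figure is about 72%, against 86%. The protocol claims no Veteran-only power.

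**Conclusion.** The point holds for the claim of sufficiency. The planned sample does not support a sex-by-treatment effect that can be separated from site and Veteran status, or from platform in the text-versus-control contrast. The interaction detectable at 80% power is about 1.05 SD, roughly twice the 0.5 SD on which the trial is sized and above the 0.69 SD of the earlier trial. This rests on an assumed two-sided 5% level and a single active arm versus control. The size conclusion barely moves with the assumed share of women at SFVAMC or with attrition; the degree of overlap does depend on that share.

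The primary randomized comparison is untouched, and the oversample roughly halves the detectable interaction (2.1 to 1.05 SD at a 6% share). More women from JMMC alone would sharpen precision further but would not remove the overlap. The protocol should correct the claim; the trial itself need not change.

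**What to change.** 1. In the Sample section, replace the sufficiency claim with the interaction the trial can detect (about 1 SD at 80% power), with its assumptions.
2. Pre-specify the subgroup comparison as an exploratory treatment-by-site contrast, JMMC non-Veteran women versus SFVAMC Veterans, and state that a difference will not be attributed to sex alone. This contrast needs no assumption about the SFVAMC split: with 66 × 0.85 / 3 = 18.7 and 45 per arm, the detectable interaction is 1.09 SD.
3. Report the randomized treatment effect within each site stratum, JMMC women and SFVAMC Veterans, with confidence intervals.
4. If Veteran-only power is quoted, give it on the protocol's any-pair basis: about 72% at d=0.5 with 45 per arm, beside 86% for the full sample.

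The cost is a few sentences and one additional pre-specified model. No change to recruitment, randomization or the primary analysis is needed. The price is a more modest claim about subgroups.
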